## **7 Dissemination of findings**

Reports on the project's progress and regular monitoring of the project activities will be provided by the FAO consultant, the Giessen PostDoc and the Principal Investigators. The research project team will be responsible to produce six-monthly progress reports, which will

- contain information on main activities and compliance with the work plan;
- identify any problems and constraints encountered during the research progress,
- provide recommendations for corrective measures;
- if necessary, revise the work plan for the following reporting period.

A contact information database will be created and maintained that will be used for group/individual mailings of paper documents and to facilitate telephone and fax communications between the Project Management, Site Management, and TAC. The project visibility will be enhanced by the launching of a FAO project website. The website will be updated at least on a 6 monthly basis.

- Lessons learnt from the project and research results will be shared through participation and presentations in relevant conferences and technical consultations regarding nutrition and feeding of infants and young children,

- preparation of research articles to be submitted to scientific journals,
- documentation of case studies, and
- preparation of guidelines and technical recommendations on improved complementary feeding using local resources.

## **8 Personnel**

The research has been developed and will be carried out by the Institute of Nutritional Sciences, Justus Liebig University Giessen, Germany in collaboration with Institute of Nutrition, Mahidol University, Bangkok, Thailand. A PhD student from Mahidol University and a PhD student from JLU-Giessen ([name]) will undertake data collection and analysis; they will be supported by MSc students from Germany and Thailand and Cambodia.

Representatives from FAO ([name]), Mahidol University, Institute of Nutrition and JLU-Giessen ([name]) will be involved in project management and technical implementation. They will provide oversight of the project's implementation, approve workplans and associate budgets, and decide upon adjustments to the project implementation strategy as required. Furthermore, they will be responsible for ensuring that information is effectively shared between FAO, Giessen and national research institutes and governments, and between country-level teams and FAO headquarters and JLU Giessen in Germany.

A Technical Advisory Committee (TAC) has been formed including researchers and practitioners from academic institutions, UN partner agencies and NGOs having been involved in similar research and/or field work on complementary feeding, behavior change and nutritional impact studies. The TAC will provide advice on the research methodology, preliminary research results and other technical issues as they arise.

At country level, the official collaboration between IMCF research group (JLU and Mahidol University) and FAO EU project will start with a common meeting on national and district level organized by FAO in May (between 28th and 31st) in Siem Reap, Cambodia. Relevant government departments and district administration/representatives will be invited. A second meeting round will be held as soon as the results of the nutrition survey are available and the cluster randomization needs to be conducted.

## 10 Annexes

## 10.1 Logical Framework of the Research Project

| Project Objectives/Research Objective                                                                                                                                                                                           | Indicators                                                                                                                                                                                                                                                                                                             | Means of Verification                                                                                     | Assumptions/Risks                                                                                                                                                                                                      |
|---------------------------------------------------------------------------------------------------------------------------------------------------------------------------------------------------------------------------------|------------------------------------------------------------------------------------------------------------------------------------------------------------------------------------------------------------------------------------------------------------------------------------------------------------------------|-----------------------------------------------------------------------------------------------------------|------------------------------------------------------------------------------------------------------------------------------------------------------------------------------------------------------------------------|
| Project Impact:
Child nutritional status is improved

Research objective:
Evaluate the impact of the project on child nutritional status in FAO food security projects                                | Key Impact Indicators: 
 
Improved child nutritional status:
 
Reduced Stunting
 
Reduced Anemia
 
Reduced vit A deficiency
 
                                                                                                                 | Baseline and Impact
Surveys of children 0-23 months in FAO food security project and non-project areas | Households are willing to participate in all aspects of data collection                                                                                                                                                |
| Outcome:
Complementary feeding (CF) practices and dietary intakes of children 0-23 months are improved

Research objective:
Assess changes in CF practices across intervention and control households | 
 
Improved CF practices (Selected WHO IYCF)
 
Decreased prevalence of anemia, vit A deficiency
 
Increased diversity of foods fed to children 6-23 months
 
Increased frequency of feeding semisolid/solid foods
 
Mothers' behavior score
 
 | One level of assessment: (Impact assessment)                                                              | The complementary feeding components are implemented according to plan and the TIPs correctly assess the decision making processes at household level that lead to sustained changes in feeding practices              |
| Output 1:
Knowledge and practices related to CF are improved                                                                                                                                                          | Knowledge and practices (breastfeeding, CF and safe handling/preparation of food, active feeding, frequency of feeding, quantity, quality) of key change agents for child feeding practices are improved.

Decreased prevalence of ARI and diarrhoea.                                                            | Two levels of assessment (TIPs and Impact assessment)                                                     | The complementary feeding components are implemented according to plan and the TIPs facilitators correctly assess the decision making processes at household level that lead to sustained changes in feeding practices |
| Project activity: Training of TIPs facilitators

Research activities:
TIPs consultants conduct the training of the TIPs facilitators according to the guidelines and                                     | TIPs facilitators are trained 
 
TIPs training is conducted according to the guideline.
 
TIPs facilitators are tested whether
 
                                                                                                                                   | TIPs training will be monitored and a pretest will be conducted and analyzed                              | Participants at the training are willing to be observed during the training and willing to                                                                                                                             |

| Project Objectives/Research Objective                                                                                                                                                                                                | Indicators                                                                                                                                                                                                                                                                                                                                                                                                                                                                                                                                                                                                                                                                 | Means of Verification                                                                                                                                                                                                                                                                                                                           | Assumptions/Risks                                                                                                                                                                                                                       |
|--------------------------------------------------------------------------------------------------------------------------------------------------------------------------------------------------------------------------------------|----------------------------------------------------------------------------------------------------------------------------------------------------------------------------------------------------------------------------------------------------------------------------------------------------------------------------------------------------------------------------------------------------------------------------------------------------------------------------------------------------------------------------------------------------------------------------------------------------------------------------------------------------------------------------|-------------------------------------------------------------------------------------------------------------------------------------------------------------------------------------------------------------------------------------------------------------------------------------------------------------------------------------------------|-----------------------------------------------------------------------------------------------------------------------------------------------------------------------------------------------------------------------------------------|
| ensures that TIPs facilitators have a common understanding of the food needs of family members most at risk of becoming malnourished and are familiarized on the approach to use when counseling the TIPs families.                  | they are familiar with nutrition education messages.
c. TIPs facilitators' capability conducting data assessment according to the TIPs guidelines is tested                                                                                                                                                                                                                                                                                                                                                                                                                                                                                                             | using the TIPs toolkit for TIPs implementation.                                                                                                                                                                                                                                                                                                 | undergo a final knowledge assessment.
TIPs Training has not been conducted in the time of the research.                                                                                                                              |
| Project activity: TIPs implementation                                                                                                                                                                                         | Behavior change messages and improved CF recipes developed and tested with mothers                                                                                                                                                                                                                                                                                                                                                                                                                                                                                                                                                                                         |                                                                                                                                                                                                                                                                                                                                                 |                                                                                                                                                                                                                                         |
| 
Research activities:
TIPs formative research generates appropriate behavior change messages and CF recipes that are:
 
Seasonally appropriate,
nutritionally adequate,
culturally acceptable
affordable.
 | 
a. # of appropriate behavior change messages developed
 
b. Assessment of the appropriateness, feasibility and acceptability of nutrition education messages
 
c. Assessment of the cultural acceptability of recipes
 
d. Assessment of the affordability of recipes
 
e. Assessment of factors affecting feeding practices and nutritional status
 
f. Assessment of facilitators/nutrition promoters' knowledge and skills in dietary counseling (in terms of accuracy of content and quality of the interaction)
 
g. Assessment of facilitators/nutrition promoters' knowledge and skills in facilitating cooking demonstrations
 | 
Research team monitoring TIPs
 
In-depth qualitative and quantitative information of TIPs and control HH
 
Cost effectiveness verified and fine tuned through Linear Programming tool.
 
Qualitative research (focus groups) on message acceptability, cultural acceptability of recipes and affordability of new recipes
 | 
TIPs has not been conducted in the time of the research and no national IYCF guidelines are available
 
Partnerships with FAO food security projects are established, funded and initiated at the same time as the research
 |
| Research activities
The potential for meeting the nutritional                                                                                                                                                              | a. Assessment of the ability of local foods to meet nutrient requirements                                                                                                                                                                                                                                                                                                                                                                                                                                                                                                                                                                                                  | Seasonal calendars of food availability developed                                                                                                                                                                                                                                                                                               | Food composition data are available for local foods (local                                                                                                                                                                              |

| Project Objectives/Research Objective                                                                                                                                            | Indicators                                                                                                                                                                                                                                                                                                                                                                                                                              | Means of Verification                                                                                                            | Assumptions/Risks                                                                                                                               |
|----------------------------------------------------------------------------------------------------------------------------------------------------------------------------------|-----------------------------------------------------------------------------------------------------------------------------------------------------------------------------------------------------------------------------------------------------------------------------------------------------------------------------------------------------------------------------------------------------------------------------------------|----------------------------------------------------------------------------------------------------------------------------------|-------------------------------------------------------------------------------------------------------------------------------------------------|
| requirements of children 6-23 months of age with locally available and affordable foods is assessed.                                                                             | by season
b. % of nutrient requirements met by improved recipes
c. Calculation of energy and nutrient density of CF
d. Number of CF recipes that meet nutritional requirements by season
e. Assessment of the cost and affordability of improved local recipes                                                                                                                                                              | Locally appropriate recipes developed

Nutrient content of CF recipes, including energy and micronutrient density assessed | food varieties) or samples of local foods or recipes are collected for laboratory analysis                                                      |
| Research activities
Improvements in dietary intakes and child nutritional status                                                                                       | a. Assessment of dietary intakes
b. Assessment of child growth
c. Assessment of motormilestones
d. Biochemical assessment of micronutrient and morbidity status                                                                                                                                                                                                                                                                | Initial and follow-up assessments of diet, growth, motormilestones and collection of blood samples                               | No drop out or refusal to participate                                                                                                           |
| Project activity –dissemination of feeding recommendations and recipes                                                                                                    | Disseminate through local community groups messages and recipes developed through TIPS                                                                                                                                                                                                                                                                                                                                                  |                                                                                                                                  |                                                                                                                                                 |
| Research Activities
Evaluate the effectiveness of disseminating behavior change messages and improved recipes for CF, in association with a food security intervention | a. Assess the process through which messages and recipes are promoted and taken up
b. Assess the factors that encourage or hinder uptake of recipes (strength of community organization, combination of FS interventions and CF interventions)
c. Assess the frequency and quality of nutrition education and dietary counseling with families and community groups
d. Assess the effectiveness of different delivery channels | Qualitative research (i.e. social mapping, focus groups discussion)

Survey assessments                                    | Presence in communities of women's groups. Messages are delivered to all persons within family/community that influence behaviors and practices |

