### 2.2.1 MALIS Project in Cambodia

In 2012 the 'Improving Food Security and Market Linkages for Smallholders (MALIS)' project will be launched in two provinces in Northern Cambodia, Otdar Meanchey and

PreahVihear, as a further continuation of the FAO EU Food Facility Project from 2009 which was implemented in ten provinces in the country. Funded by the Food Security Thematic Program(FSTP) of the EU the “Improve the Food Security of Farming Families Affected by Volatile Food Prices” project was implemented from 2009 to 2011 in 50,000 farming households who were affected by volatile food prices. The project objective was based on five aims:

- Improved agricultural productivity
- Reduce post-harvest losses
- Improve fish production and fish resources management
- Improved water resources and irrigation
- Improve dietary diversity and family feeding (focus on Infant and young children)

The target group consists of vulnerable rural families who are depending primarily on agriculture for their livelihood. With the overall objective to improve the food security and nutrition situation of the target group, a close collaboration between the Ministry of Agriculture, Forestry and Fisheries (MAFF) and local NGOs is planned. The program addresses some of the countries objectives towards food security and agricultural development as well as the Millennium Development Goal 1 and 3 (MDG) to eradicate hunger and extreme poverty in Cambodia(16). The enhancement of income, agricultural productivity and nutritional status are among the main objectives as well as the promotion of the resilience to external shocks for vulnerable smallholder farmers in targeted provinces.

As one fourth of the Cambodian population is undernourished (17), the former project also included a nutrition component. Following the TIPs formative research technique (see Chapter 2.1), the project paid special attention to the lack of knowledge in Infant and Young Child Feeding (IYCF) Practices. TIPs was conducted in 360 households of 4 villages in each of the nine provinces, one trial in the wet season (Aug - Sept 2010) and one trial in the dry season (Dec 2010 - Jan 2011). Each trial was followed by a cooking demonstration for at least 9,000 households. As a result of TIPs culturally acceptable complementary feeding practices were collected and are available for dissemination.

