With a new fund from the FSTP of the EU the present MALIS project is implemented in previous and new areas of two former target provinces, Otdar Meanchey and

PreahVihear. These provinces are considered to have a best fit to the framework established by the EU for targeting assistance under the certain program.

The expected outcome of MALIS nutrition component is that the capability of target households is to be strengthened to the extent that the diets of children below two years meet their nutritional needs by the end of the project.

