## **5 Objectives**

The purpose of this study is to observe the impact of promoting improved complementary feeding recipes and messages developed through TIPs on children's nutritional status and identify changes in complementary feeding practices in the two districts, OtdarMeanchey and PreahVihear, in Cambodia. The overall aim of the study is to evaluate the effectiveness of the wider dissemination of improved infant and young child feeding practices developed by TIPs to improve child nutritional status. The primary objective of the study is to show that children below two years have improved Height for Age Z-scores (HAZ) after at least 18 months of complementary feeding intervention, compared to children in matched control areas. Secondary objectives are to investigate whether children in the intervention area have improved nutritional status measured by vitamin A and iron status and improved health status measured by incidence of acute respiratory infection (ARI) and diarrhea compared to children in matched control areas.

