## **6 Methodology**

### **6.1 Study sites**

The intervention and control areas will be selected following the targeted area of the MALIS project in two provinces, OtdarMeanchey and PreahVihear, in Cambodia. OtdarMeanchey is divided in five districts and PreahVihear is divided in seven districts. The baseline survey will only include the target regions of MALIS.

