## 6.5 Randomization procedure

A simple randomization proportional to population per district will be conducted to select 75 survey villages for the baseline. In each village 15 households with children under two will be randomly selected. In case there are less than 15 households with children under two in the selected village, the missing number of households will be randomly selected from the closest neighbouring village. The intervention and control villages are assigned following a restricted randomization based on the results of the baseline survey.

This implies that randomization will take place after adjusting for certain variables that might interfere with variables of interest to the study. Variables of adjustment are:

- district officer
- level of stunting
- total village population
- average land holding size
- wealth status
- access to health posts, nutrition rehabilitation unit, or nutrition counseling by a NGO

The selected clusters will be the objective of randomization. Randomization will be done using the Software package “Experiment” and the operation “randomize”. The “Experiment”-package is a software extension to the statistical software  $R^{\circledast}$ . It serves to design and analyze different types of randomized trials, including cluster randomized trials, block, or matched pair designed trials (60). The baseline and the impact survey will randomly select the study participants in the selected clusters.

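### The control condition is described in two ways, and village coverage by the 2009-2011 project is not among the restriction variables

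*Protocol*

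**What the plan says.** **Comparator.** Protocol section 6.1 states: "The intervention and control areas will be selected following the targeted area of the MALIS project in two provinces". It adds: "The baseline survey will only include the target regions of MALIS". Section 6.5 then assigns the surveyed villages to intervention or control by restricted randomization. In annex 10.1, the first row of the logical framework gives the means of verification as "Surveys of children 0-23 months in FAO food security project and non-project areas", next to the research objective "Evaluate the impact of the project on child nutritional status in FAO food security projects". Section 5 sets a narrower aim: to "evaluate the effectiveness of the wider dissemination of improved infant and young child feeding practices developed by TIPs".

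**Earlier exposure.** Section 2.2.1 says that "the present MALIS project is implemented in previous and new areas of two former target provinces". The preceding FAO EU Food Facility project ran TIPs in nine provinces in 2010-11 and, according to the same section, "Each trial was followed by a cooking demonstration for at least 9,000 households". Sections 6.3.2 and 6.3.3 make the recipes and messages from that TIPs work the content of the present intervention.

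**Restriction list.** Under "Variables of adjustment are", section 6.5 names six items: district officer, level of stunting, village population, land holding, wealth, and access to health posts, a nutrition rehabilitation unit or NGO nutrition counseling. Coverage by the 2009-2011 project is not named.

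**The concern.** A village outside the project cannot belong to the sampling frame of section 6.1, so section 6.1 and annex 10.1 cannot both describe the control arm. The choice fixes what a HAZ difference means. If both arms are MALIS villages with the same food-security activities, the contrast can be credited to the nutrition messages, which is the aim in section 5. If controls lie outside the project, the contrast carries the agricultural and market support as well, and no analysis can separate the two. Even under section 6.1 the control condition is incomplete, because the protocol never says which MALIS components control villages receive.

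The second issue is narrower. Some villages eligible for the control arm may already have met the same recipes through the earlier project. If so, the contrast is diluted, and with a few dozen villages per arm the exposed villages may split unevenly by chance. The allocation scheme could prevent an uneven split, but only if the variable is on the list before villages are assigned.

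**Working it through.** **1. Comparator, section by section**

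- Section 6.1: both arms come from the MALIS target area, and the baseline survey covers MALIS regions only.
- Section 6.5: the surveyed villages are the units randomized. No step samples villages outside MALIS.
- Annex 10.1, first row: project v non-project areas, with the impact of the project as the objective.
- Annex 10.1, second row: intervention v control households.
- Annex 10.1, dissemination row: messages evaluated in association with a food security intervention, which does not say whether controls have that intervention too.

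The methods sections agree with each other. The first logframe row is the outlier. Nothing states what controls receive.

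**2. Can formerly served villages be controls?**

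Section 2.2.1 puts the earlier project in ten provinces and TIPs in nine, without listing them, and calls both MALIS provinces former targets. If the nine are among the ten, at least one MALIS province had TIPs. Since MALIS includes previously served areas, such villages can enter the frame and be assigned to control. The share is not given.

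**3. Reproducing the plan's sample size**

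Inputs from section 6.4: SDs 1.5 and 1.2 (variance sum 2.25 + 1.44 = 3.69), two-sided 5%, 80% power, m = 19, ICC 0.03.

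- With 15% of 1.96 = 0.294: n = (1.960 + 0.842)² × 3.69 / 0.294² = 335.07, matching the plan's 335. The rounded printed means (difference 0.30) give 321.8, so 0.294 is the working effect.
- DEFF = 1 + 0.03 × 18 = 1.54; 335 × 1.54 = 515.9 (516); 516 × 1.10 = 567.6 (568). Both match.
- 516 clustered children are worth about 335 independent ones, so SE = √(3.69/335) = 0.105 HAZ.

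**4. Dilution, as an upper bound**

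Assume a share q of control households already has the full effect. Power = Φ(0.294 × (1 − q)/0.105 − 1.96).

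| q (assumed) | Difference (HAZ) | Power |
|---|---|---|
| 0 | 0.294 | 80% |
| 10% | 0.265 | 71% |
| 20% | 0.235 | 61% |

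**5. Chance imbalance without restriction**

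For k villages per arm and an exposed share p, the SD of the between-arm difference in exposed share is √(4p(1 − p)/(2k − 1)). Take k from 27 (516/19) to 37 (75 baseline villages split in two) and assume p between 25% and 50%.

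- k = 37, p = 25%: about 10 percentage points.
- k = 37, p = 50%: √(1/73) = 11.7 points.
- k = 27, p = 50%: √(1/53) = 13.7 points.

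A 10-point imbalance is therefore ordinary. Its effect on the estimate, even if earlier exposure carried the whole 0.294, is at most 0.10 × 0.294 = 0.029 HAZ, or 0.029/0.105 = 0.28 of a standard error.

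**The case against.** **The design is clear from the methods.** Sections 6.1 and 6.5 provide only for MALIS villages, and the logframe looks generic: it lists TIPs facilitator training and TIPs implementation as project activities, although sections 2.2.1 and 6.3.3 report TIPs as already done. This largely stands. A reader might infer from annex 10.1 that the trial compares MALIS with villages outside it; the methods contain no such sampling. It does not remove the conflict, because the annex is protocol text naming how impact will be verified, and the silence on what controls receive remains.

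**Randomization deals with earlier exposure.** A reader might infer that the comparison is confounded by it. The documents do not support that: villages are randomized, so exposure is balanced in expectation, and chance differences between villages are part of what the standard error and ICC cover.

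**The list already has proxies.** Baseline is September 2012, after the 2010-11 demonstrations, so a lasting growth effect should show in village stunting, which is restricted on. NGO nutrition counseling is a further partial proxy, and section 6.8 has the questionnaire ask about access to FAO food security activities. These help, but none identifies coverage by the earlier project, and section 6.5 names no use of the questionnaire item in allocation.

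**The dilution scenario is extreme.** It equates a past cooking demonstration with at least 18 months of intervention. Children aged 0-23 months at an impact survey in 2014 (workplan) or 2015 (section 6.3.2) were born after the earlier project ended in 2011, so only caregivers' retained practice could carry over. This stands. Nor does the protocol show that any surveyed village was exposed: TIPs itself reached 4 villages per province, and the demonstrations are not located.

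**Conclusion.** Two limited points hold.

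1. The comparator is stated inconsistently and the control condition is not described. The methods sections favour MALIS villages in both arms, so the likely remedy is textual. The interpretation of the primary result depends on it, however, and the sections have to agree.
2. Coverage by the 2009-2011 project is missing from the restriction list although the protocol says that MALIS mixes formerly served and new areas. The consequence is possible chance imbalance (worth at most about 0.03 HAZ, or 0.28 SE, per 10 points) and dilution, not systematic bias.

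The 71% and 61% power figures should not be read as the trial's expected power. They rest on assumed exposure shares and on full carry-over, and mark the upper end of harm at those shares. The imbalance range likewise assumes that 25-50% of villages were formerly covered, a figure the protocol does not give.

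**What to change.** - Reconcile section 6.1, section 6.5 and the first row of annex 10.1 so that the control arm is described once and identically. State which MALIS components control villages receive up to the impact survey, and word the logframe objective to match the resulting contrast.
- Before villages are assigned, add to section 6.5 a yes/no variable for coverage of the village by the 2009-2011 Food Facility project or its TIPs activities. Use the same variable as a baseline covariate in the analysis, and report its distribution by arm so that any dilution is visible.

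The cost is a correction to the text, one more village-level item to obtain, and one more constraint on a restricted randomization that already has six. The gain is protection against an uneven split and a view of dilution. The allocation part cannot be added once villages have been assigned.
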